
#### Qualitative measures

*Interviews*Semi-structured interviews will be held to explore perceptions on optimal timing for support (Key objective 1) and to gain insight in possible changeable determinants of adherence to lifestyle and bodyweight recommendations. PMBC survivors will be invited for semi-structured interviews based on purposive sampling according to (non)adherence, readiness for change, and need for support over time as assessed by means of questionnaires in wave 2 and 3. The number of invited participants depends on the information that comes up during the interviews. Interviews will be guided by a topic list. Discussion topics include barriers, facilitators, and motivators for adherence to recommendations in daily clinical practice, and perceptions on optimal timing of promotion of adherence. Interviews will be audiotaped and transcribed verbatim. Transcripts from the interviews will be supplemented with field notes from the interviewer. Member checking will be performed after the interviews (i.e. returning a summary of an interview to a participant to check for accuracy and whether it resonated with their experiences) [56].*Focus groups*Focus groups will be conducted after the interviews to validate and enrich the data gathered during the interviews, to prioritize possible changeable determinants of adherence, and to further explore themes that arise during the interviews. Focus groups will be audiotaped and transcribed verbatim. Field notes from the observer will be supplemented to the transcripts. Results of each focus group will be discussed between the moderator and the observer.*Delphi-study*An iterative three-round online Delphi study will be conducted to gain insight in perceptions of medical health care professionals (i.e., mamma oncology surgeons, mamma oncology internal medics, mamma oncology nurses, oncology dieticians, oncology physical therapists, oncology psychologists), policy makers, and PMBC survivors of potential barriers and facilitators for promoting lifestyle adherence in daily clinical practice. The three rounds will be respectively used for item generation, prioritizing of items, and ranking of the items.

### Data analyses

#### Quantitative data

Descriptive statistics and Generalized Linear Mixed Models (GLMM) will be used to: (1a) longitudinally assess proportions of (non-)adherence to each recommendation, readiness for change, and the need for support, to (1b) examine sociodemographic and clinical characteristics, and to (1c) examine biological determinants, of those who do not adhere and of those in need for support over time. The relation between adherence to each recommendation and socio-demographic and non-changeable clinical characteristics will be longitudinally assessed by fitting GLMM with adherence to each recommendation (no/yes) as dependent dichotomous variable and time (wave1, wave2, wave3) and socio-demographic and clinical characteristics (age, ethnicity, socioeconomic status, marital status, stage of cancer at diagnosis, type of treatment) as independent variables. We will assess the need to include interaction terms between time and the socio-demographic and clinical characteristics. These analyses will be repeated for need for support as outcome variable. Similar analyses will be conducted for biological determinants of cancer prognosis modifiable by lifestyle and bodyweight.

With regard to aim 2a, for each single lifestyle recommendation ‘patient profiles’ will be composed by creating a cross tabulation of the variables ‘adherence to a particular recommendation’ (yes/no), ‘readiness for change’ (Not ready: pre-contemplation/contemplation; ready: preparation/action/maintenance), and ‘need for support’ (yes/no) for each time point (see “Appendix”). Based on these cross tabulations, it will be examined which patient profiles are most prevalent per time point. In addition, descriptive statistics will be used to describe changeable socio-demographic (e.g., employment, education) and clinical characteristics (e.g., tumor stage, treatment received) of the most frequent patient profiles. GLMM will be used to assess socio-demographic and clinical modifiable determinants of adherence, readiness for change, and need for support, as captured by the most prevalent patient profiles over time (aim 2b). We will assess the need to include interaction terms between time and the socio-demographic and clinical characteristics. Based on the behavior change technique taxonomy [30], the changeable socio-demographic and clinical determinants will be matched to suitable behaviour change techniques (aim 2c). Additionally, with respect to aim 2a and 2b, the composition of ‘patient profiles’, multilevel latent class modelling will be used combining adherence to all recommendations, readiness for change to each specific recommendation, and need for support for each specific recommendation, for each time point for all recommendations. The multilevel latent class model will be used to gain insight into the course of the patient profiles over time.

#### Qualitative data

Research objectives 1d and 2d, will be addressed by means of qualitative analysis. Specifically, exploring perceptions on optimal timing and method among PMBC survivors, oncology health care professionals, and other relevant stakeholders. With respect to the interviews and focus groups, a thematic analysis will be conducted as described in Braun and Clarke [57]. Transcripts will be subsequently disentangled, divided into fragments and open-coded. Codes will be categorized by subthemes and main themes. Relationships between the subthemes will be explored, to eventually cover the subthemes under the overall themes. The codes, subthemes, and themes will be discussed by two researchers until consensus is reached. Codes and (sub)themes will be structured in a code tree. The constant comparison method will be used in order to understand the differences, as well as similarities, between respondents and within each of the respondents. The main results will be discussed in the research team to enhance the robustness of the findings.

The output of the rounds of the Delphi-study (aim 1d and 2d) will be analysed (i.e., defining items, categorizing items, removal of duplicate items, calculating sum scores for prioritizing and ranking of items). Thereafter, the output will be used as input for the next round till, in consultation with the oncology medical professionals, a top rank of facilitators and barriers for lifestyle care will be created in the third round.

#### Combined data

Quantitative results obtained from the measurements and questionnaires will be combined with the qualitative results obtained from the individual interviews and focus group sessions. Together, these data sets will provide a more complete and comprehensive evaluation of optimal timing and method to enhance lifestyle in PMBC survivors (key objective 1 and 2).

### Sample size

The sample size calculation was conducted using the validated rule of thumb of a minimum of 10 participants per independent variable in the smallest group of the dichotomous outcome measure (e.g., 25% non-adherence [20, 58] vs. 75% adherence to the recommendation on alcohol intake) [59]. For aim 2b, incorporating the highest number of changeable determinants, a maximum of 16 changeable determinants will be incorporated in the analyses. Based on data on adherence to recommendations from previous studies in Dutch cancer survivors [20, 58], the largest number of participants needed to be able to detect valid associations between changeable determinants and adherence to each recommendation with inclusion of 16 independent variables is 860 for the recommendation for smoking (assuming 18.6% of women smoke) (16*10)/18.6 × 100). The required number of participants for the other recommendations are: 462 (160/34.62 × 100) for body weight; 601 (160/26.62 × 100) for physical activity; 375 (160/42.62 × 100) for foods and drinks that promote weight gain; 351 (160/45.6 × 100) for fruit intake; 580 (160/27.6 × 100) for vegetable intake; and 624 (160/25.66 × 100) for alcohol intake.

Furthermore, to be able to detect valid associations between (non-)changeable socio-demographic and clinical characteristics and the most prevalent patient profiles per time point (aim 2a and 2b), power analysis indicated a minimum of at least 1076 participants. Power analysis was based on an ANCOVA including 5 groups (expected number of main patient profiles in the cross-tabulation based on ‘adherence to a particular recommendation’, ‘readiness for change’, and ‘need for support’) and 3 covariates (e.g., stage of cancer at diagnosis), assuming a small effect for each predictor (partial eta squared = η_p_^2^ = 0.015).

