**Methods:**

The OPTIMUM-study has a mixed-methods design. To assess *optimal timing*, a longitudinal observational study will be conducted among approximately 1000 PMBC survivors. The primary outcomes are adherence to lifestyle and body weight recommendations, readiness for change, and need for support. Questionnaires will be administered at 4–6 months after cancer diagnosis (wave 1: during treatment and retrospectively before diagnosis), 1 year after diagnosis (wave 2: after completion of initial treatment), and 1.5 years after diagnosis (wave 3: during follow-up). Wave 2 and 3 include blood sampling, and either wearing an accelerometer for 7 days or completing a 3-day online food diary (randomly assigned at hospital level). To assess the *optimal method*, behavioural determinants of the primary outcomes will be matched with Behavior Change Techniques using the Behaviour Change Technique Taxonomy. Qualitative research methods will be used to explore perceptions, needs and preferences of PMBC survivors (semi-structured interviews, focus groups) and health care providers (Delphi study). Topics include perceptions on optimal timing to promote adherence; facilitators and motivators of, and barriers towards (sustained) adherence to recommendations; and acceptability of the selected methods.

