### Recruitment

Patients will be invited for study participation by their own oncology health-care professional (i.e., oncologist, internist, surgeon, or mamma care nurse) from 16 participating hospitals across the Netherlands. Eligible patients will receive an invitation letter during a visit to their oncology health care professional. After providing written informed consent, participants will be invited to complete either an online or paper version of the first questionnaire (wave 1). According to their preference for completing either an online or paper version of the questionnaire, participants will be contacted for data collection at waves 2 and 3. Participants who prefer to complete a paper version of the questionnaire will receive printed questionnaires by mail. Participants who prefer to complete an online version of the questionnaire will receive a link to the online questionnaire via e-mail. Online questionnaires will be completed via the PROFILES (Patient Reported Outcomes Following Initial treatment and Long term Evaluation of Survivorship) registry [27]. In case of non-response, one reminder will be sent per participant per wave (either via e-mail or by mail according to their preference), followed by up to 5 telephone calls. The OPTIMUM study aims to recruit approximately 1000 participants. Approximately 25 PMBC survivors will be invited for semi-structured interviews based on purposive sampling according to (non)adherence and need for support over time as assessed by means of questionnaires in wave 2 and 3.

Participants are not informed about lifestyle and body weight recommendations as part of the OPTIMUM study because of its observational nature. As such, whether or not participants are informed about the recommendations depends on the standard care they receive. Standard care for participants currently does not include information provision about lifestyle and body weight recommendations, although differences between hospitals and health care professionals do exist.

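### The recruitment target of about 1000 is 76 women short of the plan's own minimum of 1076 for the patient-profile analyses, before any loss to follow-up

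*Protocol article*

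**What the plan says.** The protocol article gives its intended size in two places. The Abstract (Methods) says that "a longitudinal observational study will be conducted among approximately 1000 PMBC survivors", and the Recruitment section says "The OPTIMUM study aims to recruit approximately 1000 participants".

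The Sample size section then sets two separate requirements:

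- **Determinants of adherence (aim 2b).** A rule of ten participants per independent variable in the smaller outcome group is applied to each recommendation. The largest result with "inclusion of 16 independent variables is 860 for the recommendation for smoking". The other six recommendations need between 351 and 624.
- **Associations with patient profiles.** These concern "the most prevalent patient profiles per time point (aim 2a and 2b". For them, "power analysis indicated a minimum of at least 1076 participants". The text explains that "Power analysis was based on an ANCOVA including 5 groups", with three covariates, "assuming a small effect for each predictor (partial eta squared = η_p_^2^ = 0.015").

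The article gives no significance level, target power or expected loss for the second calculation. The Data analyses section forms the profiles by cross tabulation separately at each time point.

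**The concern.** A minimum and a target for the same study should agree, and here the target is the lower of the two. The word used for the target is approximate, but 1076 is worded as a floor, and nothing in the article says that the lower target was chosen knowingly or which figure governs the profile analyses.

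The gap can only grow. Wave 3 comes 1.5 years after diagnosis, about a year after wave 1, and the profile analyses are repeated there on whoever still responds. A reader who takes the Sample size section at its word would credit these analyses with the precision of 1076 women, when at most about 1000 are planned at the first wave and probably fewer at the third.

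**Working it through.** **Inputs from the article.** Target N = 1000 (Abstract, Recruitment). Stated minimum N = 1076, 5 groups, 3 covariates, partial eta squared 0.015, and 860 for the smoking recommendation (all from Sample size).

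**Assumed, because the article does not give them.** Alpha 0.05. Target powers of 0.80, 0.90 and 0.95 were tried. Loss of 10%, 20% and 30% by the last wave.

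**1. The gap itself.** 1076 − 1000 = 76, and 76/1076 = 7.1%. This needs no assumption.

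**2. Where 1076 may come from.** For the group effect in an ANCOVA, df1 = 5 − 1 = 4, df2 = N − 5 − 3 = N − 8 and noncentrality λ = N·f², with f² = η²/(1 − η²).

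- Unrounded: f² = 0.015/0.985 = 0.01523, so f = 0.1234. The required N at alpha 0.05 is 789, 1017 or 1225 for power 0.80, 0.90 or 0.95.
- With f rounded to 0.12: f² = 0.0144. The required N at alpha 0.05 and power 0.90 is 1075, and power at N = 1076 is 0.9004.

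So 1076 is recovered to within one participant by a conventional choice of alpha and power with f entered to two decimals. Other combinations also come close, so this is a likely source and not a proven one.

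**3. What other sizes deliver** (alpha 0.05, df1 = 4, df2 = N − 8):

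| N | Meaning | λ, f = 0.1234 | Power | λ, f = 0.12 | Power |
|---|---|---|---|---|---|
| 1076 | stated minimum | 16.39 | 0.918 | 15.49 | 0.900 |
| 1000 | target, no loss | 15.23 | 0.895 | 14.40 | 0.875 |
| 900 | target, 10% loss | 13.71 | 0.856 | 12.96 | 0.834 |
| 800 | target, 20% loss | 12.18 | 0.806 | 11.52 | 0.781 |
| 700 | target, 30% loss | 10.66 | 0.744 | 10.08 | 0.717 |

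Before loss, the shortfall costs 0.918 − 0.895 = 0.023 or 0.900 − 0.875 = 0.025, that is 2 to 3 points of power. An assumed 20% loss costs about 11 to 12 points against the value at 1076.

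**4. What holding 1076 at wave 3 would take.** N/(1 − d) gives 1076/0.90 = 1196 recruits at 10% loss, 1076/0.80 = 1345 at 20% and 1076/0.70 = 1538 at 30%. These show the distance between the two figures; they are not a recommendation.

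**5. The other requirement.** (16 × 10)/0.186 = 860, as stated. The target exceeds it by 140, which is 14% of 1000.

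**The case against.** The best defence is that the target is approximate, that it clears the first requirement (860) with room for 14% loss, and that only the profile calculation exceeds it, at a cost of 2 to 3 points of power. The article also describes active follow-up of non-responders at every wave: a reminder, then up to five telephone calls. All of that stands, and it limits the seriousness of the point. It does not remove the contradiction. The profile requirement is a separate one, it is the larger, and it is phrased as a minimum.

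It is also fair to say that the phrase about time points attaches to the profiles and not to the number 1076. The article does not literally demand 1076 at each wave. That the number matters at each wave is an inference from the profiles being analysed there, and a reasonable one.

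A reader might go further in three ways that the article does not support:

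- *That 1076 is an arithmetic error.* Without a stated alpha and power, the printed inputs fix no sample size and so cannot contradict 1076. A standard choice with f rounded to 0.12 gives 1075. At most, the rounding makes the figure slightly conservative against 1017.
- *That sizing by ANCOVA is a fault because descriptive statistics and mixed models are planned.* Sizing on a simpler model is common, the article says openly that it did so, and no numerical consequence can be shown.
- *That the missing alpha, power and loss rate are themselves defects.* A journal article may leave these to the full protocol. They matter here only because they are needed to restate the figure.

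**Conclusion.** The point holds as an internal inconsistency: a target of about 1000 against a stated minimum of 1076 for the profile analyses of aims 2a and 2b, 76 women (7%) short with full retention and more with any loss by waves 2 and 3. The inconsistency rests on the article's own figures alone.

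Its size rests on assumptions: alpha 0.05, the group effect with 4 numerator degrees of freedom, and partial eta squared 0.015. On these, power is about 0.89 at 1000 (0.875 with f = 0.12) and 0.81 at 800 (0.78), the latter under an assumed 20% loss. The profile analyses therefore remain reasonably powered for the effect the plan names, unless loss is heavier than that. This is worth correcting but is not critical: the study is observational, and the shortfall before loss is small.

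**What to change.** Keep the enrolment target and change the text. In the Sample size section, replace the 1076 requirement with what the design delivers: about 1000 recruited, the number expected to be analysable at waves 2 and 3 under a stated loss rate, the alpha and the f actually used, and the resulting power at each wave.

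If the original calculation used alpha 0.05, 90% power and f = 0.12, the text could say that about 1000 women give power 0.875 for the five-group comparison, and that 800 remaining women would give 0.78. If the unrounded f = 0.1234 is used, the corresponding values are 0.89 and 0.81. One version of f should be chosen and used throughout, and the assumed 20% loss should be replaced by the study's own expectation or by its observed response to date.

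The cost is a few sentences. There is no extra recruitment and no change to design or analysis. The only price is that the stated power for the profile analyses becomes slightly less favourable, chiefly at the later waves.

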### Stakeholder group

A stakeholder group will be actively involved throughout the study, in order to provide a solid basis for implementation and dissemination of study findings. This group consists of 10–15 stakeholders, including representatives of: the Dutch breast cancer patient association, professional bodies for health care professionals such as oncologists, oncology nurses, and general practitioners; policy makers, and a representative of health insurance companies. Stakeholders will be: informed about study progress, consulted for advice on issues that may arise throughout the study, involved in decision making, and in writing a plan for adoption, implementation, sustainability, and evaluation of guidelines on how and when to promote adherence. In addition, stakeholders will be consulted individually by telephone or e-mail when necessary.

### Ethical considerations

The study protocol has been reviewed and approved by the medical research ethics committee METC Brabant (Medical Research Ethics Committee Brabant, the Netherlands, reference number: NL66913.028.18). In addition, the study has been reviewed and approved by the local ethics committees of the participating centers.

### Data security/disclosure of original documents

Confidentiality and anonymity of participants will be guaranteed by assigning a study number to each participant. All collected data will all be stored in a secured location for 15 years.

## Discussion

In most PMBC patients lifestyle and bodyweight are suboptimal [1, 17–22], which may be related to unhealthy lifestyle behaviors. The OPTIMUM-study aims to provide scientific evidence on *when* and *how* to promote sustained adherence and in *which* PMBC patients. The study leads to products (i.e. a toolbox) that can be used in clinical practice to promote sustained adherence to lifestyle and bodyweight recommendations in PMBC patients.

### Trial status

The inclusion of patients started in February 2019. Patients will be followed up for 1.5 years after diagnosis. The COVID-19 pandemic has delayed the inclusion of PMBC survivors in the OPTIMUM-study.

## Data Availability

After finishing the data collection, the data will be freely available for non-commercial scientific research, subject to study question, privacy and confidentiality restrictions, and registration (www.profilesregistry.nl).

## Appendix: Overview of the categorization of cancer survivors into ‘Patient Profiles’ according to adherence to a particular WCRF-recommendation, stage of change, and perceived need for support.

**Table Taba:**

**Stage of change** [29]		Adherence to a particular WCRF-recommendation	
		Does not meet recommendation	Meets recommendation
*Not ready for change*			
*Precontemplation* (*not ready*): not intending to take action in the next six months	No need for support	Cancer survivors who do not meet a WCRF-recommendation, do not intend to change their behavior, and do not perceive a need for support	Cancer survivors who meet a WCRF-recommendation, do not intend to change their behavior, and do not perceive a need for support
	Need for support	Cancer survivors who do not meet a WCRF-recommendation, do not intend to change their behavior, and perceive a need for support^a^	Cancer survivors who meet a WCRF-recommendation, do not intend to change their behavior, and report a perceived need for support^a^
*Contemplation* (getting ready): intending to take action in the next 6 months	No need for support	Cancer survivors who do not meet a WCRF-recommendation, intend to change in the foreseeable future, and do not perceive a need for support	Cancer survivors who meet a WCRF-recommendation, intend to change in the foreseeable future, and do not perceive a need for support
	Need for support	Cancer survivors who do not meet a WCRF-recommendation, intend to change in the foreseeable future, and perceive a need for support	Cancer survivors who meet a WCRF-recommendation, intend to change in the foreseeable future, and perceive a need for support
*Ready for change*			
*Preparation (ready)*: ready to take action in the next 30 days	No need for support	Cancer survivors who do not meet a WCRF-recommendation, intend to take action in the immediate future, and do not perceive a need for support	Cancer survivors who meet a WCRF-recommendation, intend to take action in the immediate future, and do not perceive a need for support
	Need for support	Cancer survivors who do not meet a WCRF-recommendation, intend to take action in the immediate future, and perceive a need for support	Cancer survivors who meet a WCRF-recommendation, intend to take action in the immediate future, and perceive a need for support
*Action*: has made overt lifestyle changes in the past 6 months	No need for support	Cancer survivors who do not meet a WCRF-recommendation, but have made overt lifestyle changes in the past 6 months, and do not perceive a need for support	Cancer survivors who meet a WCRF-recommendation, have made overt lifestyle changes in the past 6 months, and do not perceive a need for support
	Need for support	Cancer survivors who do not meet a WCRF-recommendation, but have made overt lifestyle changes in the past 6 months, and who perceive a need for support (to maintain lifestyle changes)	Cancer survivors who meet a WCRF-recommendation, have made overt lifestyle changes in the past 6 months, and who perceive a need for support (to maintain lifestyle changes)
*Maintenance*: doing a new behavior for more than six months	No need for support	Cancer survivors who do not meet a WCRF-recommendation, but have been maintaining lifestyle changes for at least 6 months, and who do not perceive a need for support	Cancer survivors who meet a WCRF-recommendation, have been maintaining lifestyle changes for at least 6 months, and who do not perceive a need for support
	Need for support	Cancer survivors who do not meet a WCRF-recommendation, but have been maintaining lifestyle changes for at least 6 months, and who perceive a need for support to maintain their changes	Cancer survivors who meet a WCRF-recommendation, have been maintaining lifestyle changes for at least 6 months, and who do not perceive a need for support to maintain their changes

^a^Unlikely scenario, expected cell-frequency of near zero.

